### Outcomes Assessed

The primary outcome will be ischemic stroke volume, measured by automated planimetric method on FLAIR imaging sequences of MRI performed 3 months after index event. The secondary outcomes are presented in Table 2. Neuroimaging assessment will include analysis of the three MRI performed during the study: before treatment, 48 h after treatment, and at 3 months. The neuroradiologist that will evaluate lesion volumes and physicians that will evaluate the secondary outcomes will not be involved in the initial management of the patient nor intervention and will be blinded for treatment allocation.

**Table 2 T2:** Study outcomes assessed.

Primary outcome
Ischemic stroke volume on magnetic resonance imaging (MRI) performed at 3 months

**Secondary outcomes**

Hemorrhagic transformation (defined as type 2 parenchymal hemorrhage) Evolution of ischemic stroke volume from pre-treatment MRI to control MRI (48 h after intervention). Any stroke (ischemic stroke, intracerebral hemorrhage, and subarachnoid hemorrahge) Death of any cause Functional outcome at 3 months: mRS Impact of stroke throughout the first 3 months: Stroke Impact Scale Cognitive performance at 3 months: Montreal Cognitive Assessment scale (MoCA) Functional Independence at 3 months: Barthel Scale Upper limb Capacity at 3 months: Stroke Upper Limb Capacity Scale Mood at 3 months: Hospital Anxiety and Depression Scale Quality of life at 3 months: EuroQol Scale (EQ-5D) Gait speed at 3 months (10 m test) Temporo-spatial gait organization at 3 months (GAITRIte speed) Deglutition at 3 months: Functional Oral Intake Scale Language: Aphasia Rapid Test

### Data Monitoring Board

An independent Data and Safety and Monitoring Board (DSMB) will monitor any serious adverse events. It will be constituted by Neurologists and Internal Medicine physicians not involved in any part of the study design or execution. In the event of any safety concern, namely, rate of hemorrhagic transformation, cancer, procedural complications, or any other unexpected serious adverse event regarding the intervention group, the DSMB will make a recommendation to continue, stop, or modify the trial.

### Ethics

A signed written informed consent form will be sought by co-investigator stroke physicians and mandatory for participation in the trial. In the form all study procedures, potential risks and benefits are explained in simple terms. The study physicians will be responsible to explain and make sure the protocol is correctly understood by participants. All study subjects will be free to withdraw consent at any time. In case the patient is handicapped and not able to write down the required information, a legally acceptable representative will be allowed to fill out the informed consent form. Participants will be given a study number, which will be kept throughout all the analysis, maintaining confidentiality. All study participants will have a prespecified insurance to cover any adverse event of study participation.

Possible safety concerns rely on MRI acquisition, bone marrow aspiration, and angiographic catheterization (that will all follow routine protocols), as well as the autotransplant of CD34+ (that has been suggested to be safe in a phase I trial). Clinical follow-up after study completion will be the discretion of the treating physician.

An additional ethical concern will be to maintain blinding of the participants throughout the trial. Apart from the above mentioned design, all study and hospital staff personnel will receive training specific to this trial.

The study will be conducted in accordance with the principles of Good Clinical Practice, the Medical Research Involving Human Subjects act and the Declaration of Helsinki. The study has been approved by the funding body (COMPETE 2020, Ref: 3386). All protocol changes such as modifications in eligibility criteria, outcome measures, analyses, or study procedures will be resubmitted.

### Sample Size Estimates

No human randomized trials are available for effect estimate on intra-arterial administration of CD34+ for acute ischemic stroke. Moreover, animal studies are not ideal considering the specificity and inherent heterogeneity of human subjects. As such, for sample size calculation, we have used data from human observational studies on EPCs (7, 13). These studies indicated a large effect of EPCs in final ischemic lesion volume, with reported treatment effect sizes ranging from 1.2 to 2.0 (7, 13). For our sample size calculation of a unicenter pivotal phase IIa trial, we used an effect size of 1.2 for 90% power and a significance level of 5% to identify a difference between independent means of final infarct volume. A total of 30 patients was estimated for the trial: 10 patients treated at day 7 ± 2, 10 at day 20 ± 5, and 10 in the control group (5 sham procedures at each timepoint to ensure blinding).

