**Sample size estimates:**

30 patients will be randomized for a power of 90% and alpha of 0.05 to detect a difference in 3 months infarct volume.

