## Methods and Analysis

### Design

STROKE34 is a phase IIa superiority, unicenter, randomized, blinded outcome assessment, sham-controlled clinical trial evaluating the efficacy of intra-arterially administered CD34+ cells 7 ± 2 and 20 ± 5 days after ischemic stroke (PROBE design).

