### Randomization

Subjects will be randomized, stratified for age, gender, baseline NIHSS (at randomization), laterality and performance of recanalization therapies (intravenous or intra-arterial) into intervention at day 7 ± 2; intervention at day 20 ± 5; sham procedure at day 7 ± 2; sham at day 20 ± 5, in a 2:2:1:1 ratio, using a computerized stratified randomization program (Figure 1).

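### The stated 90% power gives neither sidedness nor contrast; two-sided, no unadjusted comparison among the 10/10/10 groups reaches it (about 85% pooled, about 72% per window)

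*Protocol article*

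**What the plan says.** The abstract's sample size paragraph states that "30 patients will be randomized for a power of 90% and alpha of 0.05 to detect a difference in 3 months infarct volume". The Sample Size Estimates section gives the inputs: "we used an effect size of 1.2 for 90% power and a significance level of 5% to identify a difference between independent means". The outcome compared is infarct volume at 3 months. The value 1.2 is the lower end of what the section takes from observational studies, "with reported treatment effect sizes ranging from 1.2 to 2.0". It continues "A total of 30 patients was estimated for the trial", with 10 patients treated at day 7, 10 at day 20 and "10 in the control group (5 sham procedures at each timepoint to ensure blinding"). The Randomization section matches this split, allocating "in a 2:2:1:1 ratio" to the two active and two sham arms.

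The Design section describes a "phase IIa superiority, unicenter, randomized, blinded outcome assessment, sham-controlled clinical trial". No section says whether the 5% is one- or two-sided, or whether the powered comparison is pooled active against sham, each window against sham, or an overall three-group test. The Expected Results section anticipates lower volumes with the autotransplant as a whole. The Discussion also hopes to learn which of the two windows is preferable.

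**The concern.** The inputs describe a comparison of two means, but the trial has three groups of 10. A power figure means something only for a named comparison, and the comparisons this design allows differ widely in power.

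90% is the only operating characteristic that the article gives, and it stands without qualification in the abstract. A reader who takes it at face value will assume a 10% chance of missing a 1.2 SD effect, including for the window-level questions. For each window against sham that chance is 28% two-sided (100 − 71.8) and 17.5% one-sided (100 − 82.5). A null result for one window would then count for more than it should, in a trial meant to inform the choice of window for phase III.

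**Working it through.** **Inputs.** Standardised difference d = 1.2, α = 0.05, power 90%, N = 30, groups 10/10/10 with the shams combined (Sample Size Estimates; allocation ratio from Randomization). Sidedness and contrast are not stated, so each is varied.

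**1. Reproducing the 30.** Two routes lead to it.

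- Two equal groups, two-sided, normal approximation: n per group = 2(1.960 + 1.2816)² / 1.2² = 14.6, so 15, and 2 × 15 = 30. By t-test, 15 per group gives 88.7%, and 16 per group (total 32) is the smallest size reaching 90% (90.7%). This route gives the total but not the trial's split.
- Pooled active against sham at 2:1, one-sided 5%, t-test: the smallest size reaching 90% is 20 + 10 = 30 (91.6%). This route gives both the total and the split.

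The document does not say which was used, if either.

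**2. Power of the comparisons that the design allows.** For the two-sample t-test the noncentrality is d·√(n₁n₂/(n₁+n₂)) with n₁+n₂−2 degrees of freedom.

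- 10 v 10: 1.2 × √(100/20) = 2.683, df 18.
- 20 v 10: 1.2 × √(200/30) = 3.098, df 28.

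| Comparison at d = 1.2 | Two-sided 5% | One-sided 5% |
|---|---|---|
| Pooled active v sham, 20 v 10 | 84.9% | 91.6% |
| One window v sham, or day 7 v day 20, 10 v 10 | 71.8% | 82.5% |

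The normal approximation does not rescue the two-sided figures: 87.3% for 20 v 10 and 76.5% for 10 v 10.

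A three-group F test with both active groups 1.2 SD from sham has group means 0, 1.2, 1.2 and grand mean 0.8. So λ = 10 × (0.64 + 0.16 + 0.16) = 9.6 on 2 and 27 df, which gives 74.9%.

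**3. What 90% would need, two-sided.** With 10 v 10, an effect of 1.53. With 20 v 10, an effect of 1.30. At d = 1.2 and 2:1 allocation, 24 + 12 = 36 patients.

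**4. Sensitivity to missing outcomes.** The article gives no loss rate, so 10% is an assumption. With 18 v 9 the noncentrality is 1.2 × √(162/27) = 2.939 on 25 df. Power is 80.7% two-sided and about 89% one-sided. The one reading that supports 90% therefore has little slack.

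**The case against.** The strongest reply is that 90% may be correct as intended. The article calls the trial a superiority trial and expects lower volumes with the autotransplant as a whole. A one-sided 5% pooled test needs exactly 30 patients in exactly the stated 20:10 division. This stands, and it rules out a flat claim that 90% is not delivered. It does not settle the matter: the reading requires two choices that the text does not state, the wording refers only to a difference, and an unqualified 5% is normally read as two-sided.

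A reader might also infer that the 30 is simply a two-group requirement (15 + 15) divided by mistake among three groups. The numbers allow this but do not show it, because the one-sided pooled route gives 30 as well. Nor should power be quoted for an active arm against its same-window sham (10 v 5). The plan defines one control group of 10 and splits the shams by timepoint only to protect blinding.

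Three further points are fair.

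- 1.2 is the lower end of the reported range, and at d = 1.5 the pooled two-sided power is 96%. But the 90% is stated for 1.2.
- Adjusting for pre-treatment volume could bring the pooled two-sided comparison to 90% if its correlation with the 3-month volume were about 0.4 (assumed), since 1.2/√(1 − 0.16) = 1.31 exceeds the required 1.30. But the sample size section describes no adjustment.
- The Discussion calls the trial exploratory and concedes its small size, which softens the harm. The sample size section, however, also calls it pivotal, and the abstract gives 90% without caveat.

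**Conclusion.** The concern holds in conditional form. As written, the 90% is attached to no contrast and no sidedness. Read two-sided, it is met by no unadjusted comparison at d = 1.2: the shortfall is about 5 percentage points for the pooled contrast (84.9%) and about 18 for each window against sham and for window against window (71.8%). It is met only by a one-sided 5% pooled comparison with essentially complete data. For the window-level questions it is met on neither sidedness.

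These figures assume normally distributed outcomes with a common SD, t-tests at an unadjusted 5%, and all 30 patients evaluable unless stated otherwise. How the 30 was derived remains unknown.

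**What to change.** Keep 30 patients. In the Sample Size Estimates section and the abstract, name the primary contrast and its sidedness, and restate the power to match. Pooled active against pooled sham gives the most power.

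- If the test is two-sided, replace 90% with about 85% for the pooled contrast at an effect size of 1.2, and add that it falls to about 81% under an assumed 10% loss.
- If a one-sided 5% pooled test was intended, say so. The 90% can then stand for that contrast with all 30 evaluable (91.6%), with a note that it becomes about 89% under the same assumed loss.
- In either case, report the power for each window against sham and for day 7 against day 20: about 72% two-sided, 82.5% one-sided.
- If the authors rely on a baseline-adjusted analysis, recompute the power for it and state the assumed correlation.

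The cost is revised wording and, on the two-sided reading, a less favourable stated power. No patients are added and trial conduct does not change.

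### The primary endpoint is defined and sized as unadjusted 3-month infarct volume; unless the full plan already does so, the primary analysis should adjust for the pre-treatment volume that the trial already plans to measure

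*Protocol article*

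**What the plan says.** All references are to the protocol article.

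- **Endpoint.** The definition reads "The primary outcome will be ischemic stroke volume, measured by automated planimetric method on FLAIR imaging sequences of MRI performed 3 months after index event" (section Outcomes Assessed). Table 2 repeats it: "Ischemic stroke volume on magnetic resonance imaging (MRI) performed at 3 months". It is an absolute volume, not a change, a ratio or a baseline-adjusted value.
- **Sizing.** Under Sample Size Estimates, the stated aim of the calculation is "to identify a difference between independent means of final infarct volume". Its inputs are given in these words: "we used an effect size of 1.2 for 90% power and a significance level of 5" per cent. The effect comes from observational studies "with reported treatment effect sizes ranging from 1.2 to 2.0". The total is 30: 10 treated at day 7 ± 2, 10 treated at day 20 ± 5, and 10 shams, five at each timepoint.
- **Imaging.** Outcomes Assessed: "Neuroimaging assessment will include analysis of the three MRI performed during the study: before treatment, 48 h after treatment, and at 3 months".
- **Use of the pre-treatment volume.** In Table 2 it enters one secondary outcome, the evolution of lesion volume from before treatment to 48 hours after the intervention.
- **Randomization.** The stratification factors are age, gender, baseline NIHSS, laterality and recanalization therapy. Lesion volume is not one of them.

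The article names no statistical model, covariate or transformation for the primary endpoint.

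**The concern.** Treatment starts days to weeks after onset, when the infarct is already present and due to be imaged. Patients who start with a large lesion can be expected to have a large lesion at 3 months, so part of the between-patient spread in final volume was there before any cells were given. An unadjusted comparison of final means counts that part as noise, and it lets a chance difference in starting volume pass into the estimated treatment effect.

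This matters more than usual here. The Discussion defends the small sample on the ground that an imaging endpoint needs fewer patients, an argument that depends on precision. Pre-treatment volume is an obvious source of precision that the trial already plans to measure, yet the article gives it no role in the primary comparison.

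**Working it through.** **Inputs from the article.** Standardised effect d = 1.2; power 90%; significance level 5% (sidedness not stated, taken as two-sided); allocation 2:2:1:1, so 20 active and 10 sham if the windows are pooled. The abstract makes the same claim: "30 patients will be randomized for a power of 90% and alpha of 0.05 to detect a difference in 3 months infarct volume".

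**Assumed inputs.** The correlation r between pre-treatment and 3-month volume is not given; 0.3, 0.5 and 0.7 are shown. The article does not say which contrast is primary; the pooled active-versus-sham contrast is used.

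**1. Reproduce the plan's figure.** For two equal groups, unadjusted, by the normal formula:

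n per group = 2 × (1.960 + 1.282)² / 1.2² = 14.6, rounded up to 15, so 30 in total.

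The stated total therefore comes out of an unadjusted two-group comparison, which confirms that the sizing makes no use of starting volume. That 30 fits two groups of 15 better than three of 10 is a separate matter and is not relied on here.

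**2. Unadjusted power, pooled 20 v 10.** Noncentrality = d × √(20 × 10 / 30) = 1.2 × 2.582 = 3.10. With 28 degrees of freedom and a two-sided 5% t-test, power is 85%.

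**3. Effect of adjustment.** ANCOVA multiplies the residual variance by (1 − r²), so the effective effect is d / √(1 − r²). Each active arm lies wholly in one window and the shams are split five and five. Treatment is therefore balanced across windows (10 active to 5 sham in each), and a window term does not inflate the variance of the pooled contrast. Window and baseline volume together cost two degrees of freedom, leaving 26.

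| Assumed r | Residual variance removed (r²) | Effective d | Noncentrality | Power, 20 v 10 |
|---|---|---|---|---|
| none (unadjusted) | 0% | 1.20 | 3.10 | 85% |
| 0.3 | 9% | 1.26 | 3.25 | 88% |
| 0.5 | 25% | 1.39 | 3.58 | 93% |
| 0.7 | 49% | 1.68 | 4.34 | 99% |

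With 27 degrees of freedom (baseline only) the rounded powers are the same.

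**4. Price if the covariate is useless.** At r = 0 with 26 degrees of freedom, power is still 85% after rounding (84.7% against 84.9%).

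**The case against.** The strongest objection is that the sentence on independent means describes how the sample size was calculated, not how the data will be analysed. The article has no analysis section, and covariates and transformations usually sit in a full protocol or SAP, neither of which is shown. Sizing on an unadjusted comparison is also common, and conservative if adjustment follows. All of this stands. A reader might infer that the sponsor has chosen to ignore starting volume; the article does not support that, and its silence on the model is not a fault in itself. What remains is that the endpoint and the sizing are both set out in unadjusted form, while the one named use of pre-treatment volume lies elsewhere.

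Several stronger readings should also be resisted:

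- **That most of the obtainable precision is thrown away.** More than half the variance is removed only if r exceeds about 0.71 (0.71² ≈ 0.50), and no figure in the article supports such a value.
- **That adjustment restores 90% power for each active arm against all 10 shams.** Unadjusted 10 v 10 power is 72%, and it reaches about 94% at r = 0.7 if there is no window term. With window in the model, a single arm is identified only against its five same-window shams, and power at r = 0.7 is about 82%.
- **That skewness costs a known amount of power.** Such figures need an assumed distribution and place the effect of 1.2 on the log scale, whereas the article applies it to mean volume.
- **That a 7-day versus 20-day contrast could be adjusted for a volume obtained within 7 days in everyone.** The article does not fix the timing of the pre-treatment MRI and does not show that such a volume will exist for all patients.

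**Conclusion.** The point holds as an inexpensive improvement, not as an error or contradiction. The endpoint is absolute 3-month volume, the sample size rests on an unadjusted difference in means, and the planned pre-treatment MRI has a named role only in a 48-hour secondary outcome.

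The gain depends on r, which the article does not give: modest at 0.3 (three percentage points of power) and substantial at 0.7 (about 14). At r = 0.5 the pooled comparison passes the planned 90%; at 0.3 it falls just short. These figures assume the pooled 20 v 10 contrast, a two-sided 5% test, the planned effect of 1.2 SD, 30 evaluable patients, and a linear relation with the same slope in both windows. If the full protocol or SAP already adjusts for pre-treatment volume, all that remains is to say so beside the sample size.

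**What to change.** Unless the full protocol or SAP already does so, specify before unblinding:

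1. The primary analysis is an ANCOVA of 3-month FLAIR volume on active versus sham, with treatment window (7 or 20 days) and pre-treatment volume as covariates. If volumes are expected to be skewed, put both volumes on the log or cube-root scale and fix that choice in advance.
2. Window stays in the model because the pre-treatment MRI may fall at a different stroke age in the two windows. State when that MRI is done relative to onset and to the procedure.
3. The unadjusted comparison of final volumes is kept as a sensitivity analysis.
4. Sample Size Estimates notes that the calculation is unadjusted and shows power over a range of r.

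The cost is a change of wording and one or two degrees of freedom. The pre-treatment MRI is already planned, so no scan, visit or patient is added.

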### Expected Results

The authors expect that the autotransplant of CD34+ will be associated with lower infarct volumes at 3 months. Observational and *in vitro* data do not allow a rational expectation regarding the optimal time window for CD34+ administration (7 ± 2 vs. 20 ± 5 days). Considering the validated cellular protocol using autotransplantation and angiographic delivery using routine catheterization techniques, we expect to confirm the overall safety of this procedure, with no serious adverse events.

### Dissemination and Data Availability

The results will be disseminated through peer-reviewed publications, presentation at relevant scientific conferences and the general public.

The datasets generated during the study will be available on reasonable request.

## Discussion

The potential integration of stem cells in the treatment algorithm of acute ischemic stroke is still limited by several uncertainties, with most data coming from observational studies. STROKE34 is a randomized trial comparing different timepoints of CD34+ autotransplant: subacute (7 days) and late subacute stages (20 days). CD34+ have been confirmed to have a contributing role in the development of angiogenesis *in vivo* and *in vitro*. Angiogenesis plays a pivotal role in poststroke recovery; however, animal models have raised the possibility of hemorrhagic transformation as a potential complication of promoting new, immature vessels (14). Nonetheless, this link shows an apparent time-dependent response with acute disruption of the blood–brain barrier and hemorrhagic transformation in the first hours after stroke, whereas enhancing effective neoangiogenesis with improved outcomes in the subacute stage (8, 15). These facts reinforce the need to define an optimized therapeutic window for the design of future phase III trials.

Three methods are potential candidates for delivery of CD34+ cells: surgical cranial implantation, intravenous, and intra-arterial. Considering the invasiveness and potential hazards of surgical implantation as well as the significant absorption by non-target organs with intravenous delivery, intra-arterial administration seems to be the most promising candidate. This method is further supported by the increasing use of intra-arterial access for the treatment of acute stroke, and the safety and feasibility demonstrated in phase I study (10).

Another critical point in the design of this trial is the choice of therapeutic time window. Angiogenesis after stroke has been demonstrated from 3 to 4 days up to 5 weeks after injury (16–18). However, it is still unknown when CD34+ transplantation would be clinically effective. Early administration would imply exposing the highly active and metabolically demanding CD34+ cells to an inhospitable ischemic environment and would potentially promote ineffective angiogenesis and hemorrhagic transformation. Moreover, within the first 24 h, bone marrow aspiration would be contra-indicated in patients submitted to intravenous thrombolysis. Nonetheless, it is uncertain if later time windows would still have any clinical meaning, and the need for a permeable blood–brain barrier will ultimately limit cell delivery beyond the first 5 weeks (19). Altogether, a wide time frame is still potentially usable (from the first days up to 5 weeks) with presumably different biological effects and clinical implications. In this trial, we hope to answer if an earlier time window (5–9 days) is preferable compared to a later window (15–25 days).

A potential limitation of this study design is the small sample size planned. However, we have defined the primary endpoint as a neuroimaging variable (3 months infarct volume), to allow the inclusion of a smaller number of patients in this exploratory phase IIa trial, and have included comprehensive functional assessments as secondary outcomes.

